### Ethical and academic management

The research protocol was reviewed and approved by the Ethics Committee of Southwest Medical University, and we will not begin recruiting at other centers in the trial until local ethical approval has been obtained. The ethics committee will be responsible for supervising all procedures of the study. Prior to making any changes to the study protocol, a written application will be submitted to the ethics committee for approval, and new written informed consent will be obtained from the guardians.

An independent academic board, which is composed of competent department, data monitoring, and safety management advisors, has been implemented to oversee unwanted effects and risks, as well as the collection and management of the data. The academic board will review all research data every 3 months. Until the included patients are discharged, each potential adverse effect will be monitored and reported to the academic board within 48 h. All members of the academic board are independent of the sponsor and trial investigators and free of competing interests.

Participants, as well as the researchers, evaluators, doctors, and nurses who are responsible for screening, recruitment, dispensing medicine, and outcome assessment, will remain blinded to treatment allocations. The researchers conducting the statistical analysis will know only the group codes but not the corresponding interventions. When severe adverse effects occur, the academic board has the right to unseal emergency envelopes. The reason for unblinding and time will be recorded. We prepared an insurance policy for every participant. This will provide ancillary and posttrial care in the case of any harm resulting from participation in the clinical trial.

After consulting the academic board, the treatment will be suspended for the following conditions: (1) serious adverse reactions (death or severe infections) that occur during the testing or (2) a guardian request withdraw their infant from the study at any time and without any consequences. The primary outcome and other data collected for participants until the date of withdrawal will be used and analyzed as part of the ITT population.

Patients and the public were not involved in the design of the present study. The results of the trial will be published in a peer-reviewed journal and will be presented at national and international conferences. The final author’s confirmation will be based on the contribution to the study and there are no plans to utilize professional writers.

### Quality control

To ensure a full understanding and mastery of the standard operating procedures, all researchers will be trained before the trial begins. Independent investigators at the Affiliated Hospital of Southwest Medical University will regularly monitor the quality of the data collected on the CRFs. If any error exists, researchers will be notified immediately.

## Discussion

In babies < 26^+0^ weeks gestational age, several problems, such as PDA, severe apnea, and high thorax compliance, may lead to noninvasive respiratory dependency at day 28 without any link to BPD. Furthermore, a higher rate of sepsis was observed in infants born at 24–25 weeks gestational age who were treated with hydrocortisone in a previous study [21]. Therefore, we will restrict the eligible patients to those between 26^+0^ and 30^+6^ weeks gestational age.

Because inflammation plays a key role in BPD, postnatal glucocorticoids are thought to be the most effective therapeutic strategy for preterm infants with a high risk for developing BPD [35], but they are accompanied by severe long-term adverse neurodevelopmental outcomes [11, 12]. These adverse outcomes seem to be associated with the timing of steroid exposure and the cumulative dosage of glucocorticoids; the earlier the treatment initiation and/or the larger the dosage, the higher the risk of adverse outcomes [11, 15].

Following the actual recommendations, many infants presenting with early BPD do not receive any anti-inflammatory therapy, and a high percentage of premature infants are still oxygen-dependent or on respiratory support at 36 weeks PMA (moderate or severe BPD) [27–29], which is associated with poor long-term pulmonary outcomes, including home oxygen therapy and a high rate of bronchopulmonary infections and rehospitalization [2]. A recent study showed that moderate or severe BPD at 36 weeks PMA was associated with increased mortality in the first year of life and moderate to severe neurodevelopmental impairment (55%) [6]. Thus, we hypothesize that anti-inflammatory treatment of infants meeting the NICHD criteria for BPD at 28 days of life may decrease the incidence of moderate or severe BPD at 36 weeks PMA and reduce long-term adverse outcomes.

In previous studies, early low-dose HC therapy in ventilator-dependent infants improved the rate of survival without BPD at 36 weeks PMA [21] without adverse neurodevelopmental outcomes at 2 years of age [22, 24]. Thus, it seems reasonable to use low-dose HC to treat infants with early BPD to improve pulmonary outcome. Accordingly, the efficacy and safety of this treatment must be proven by a randomized controlled trial.

## Trial status

Data collection will begin from August 1, 2019, and will end in July 31, 2022. The protocol version number and date are as follows: Second Edition, 13 March, 2019.

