### Study design

This multicenter double-blind randomized controlled trial will be performed at three centers in China. The enrollment period will be 1 year, and there will be a series of follow-up for every child until 2 years corrected age, which is the revised age from the 40th gestation week for a premature baby. The human research ethics committees at each participating center approved the trial, and an independent academic board will monitor the trial.

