### Randomization

Eligible patients will be randomized at day 28 after birth in each center after at least one guardian provides informed consent. A list of all eligible patients not included in the study will be provided from all centers throughout the time of enrollment. This trial will be protected from selection bias by using concealed, stratified, and blocked randomization. Randomization will be stratified according to gestational age stratum (26^+0^ to 28^+6^ weeks, and 29^+0^ to 30^+6^ weeks) in each study center. Multiple birth infants will be internally randomized. The randomization procedure will be generated by using Excel software by the GCP faculty at the participating hospitals, and it will be sealed in a sequentially numbered envelope to maintain the allocation concealment. According to the allocation sequence, drug packages will be hidden and labeled sequentially. Participants will receive packaged drug in the order of recruitment. The first dose of study medication will be administered within 1 h after randomization.

The complete random sequence will be kept by the primary researcher at the affiliated hospital of Southwest Medical University. Centers will individually have emergency envelopes that contain the treatment information for patients. Emergency envelopes can be unsealed only under special conditions.

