#### Long-term outcomes after hospital discharge

Neurodevelopmental impairment at 104 weeks corrected age: The Bayley Scales of Infant and Toddler Development, Second Edition (BSID II) will be used in this trial.
Cognitive delay: defined as a cognitive score less than 80.Language delay: defined as a language score less than 80.Cerebral palsy and severity of cerebral palsy using the gross motor function classification system.Hearing loss requiring hearing aids at 104 weeks corrected age.Blindness at 104 weeks corrected age: vision loss with only form or shadow vision or no useful vision.Number of readmissions in the first year since the first discharge home.Weight, length, and head circumference at 40 weeks postmenstrual age and 12, 26, 52, and 104 weeks corrected age.Premature birth-related mortality from enrollment to 104 weeks corrected age.Behavioral problems (child behavior checklist) at 104 weeks corrected age. The scores on the checklist will be compared between groups.

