### Clinical data collection

At the time of randomization, baseline data will be collected from all included patients, including maternal and patient characteristics. Demographic data will include sex, birth weight, gestational age, 5-min Apgar score, surfactant therapy, prenatal corticosteroid use, premature rupture of the membrane before the onset of labor (> 18 h), singleton/multiple birth, and mode of delivery. Population characteristics will be used to compare outcomes between the two groups.

The following clinical data will be collected: continuous positive airway pressure (CPAP)-assisted time, invasive ventilator-assisted time, days of hospitalization, days on supplemental oxygen, IVH, spontaneous intestinal perforation, NEC, and ROP.

During HC treatment, respiratory support, blood sugar, blood pressure, and anthropometric data will be collected. Outcome variables and cointerventions will be recorded at 36 weeks PMA.

After discharge, one trained investigator in each center will follow up all patients at 40 weeks PMA and at 12, 26, 52, and 104 weeks corrected age. We will provide free neurodevelopmental impairment examinations to promote follow-up rates. For potential dropouts during the follow-up, we will expand the sample size by 20% and the missing data will be ignored in the analysis. The outcomes at each time point mentioned above will be collected by the investigators (Table 1).

**Table 1 Tab1:** SPIRIT figure: showing time points for enrollment, interventions, and assessment

	Study period						
	Enrollment	Allocation	Post-allocation				Close-out
Time point	At 4 weeks after birth	At 4 weeks after birth	At 36 weeks postmenstrual age	At 40 weeks postmenstrual age	At 12, 26 weeks corrected age	At 52 weeks corrected age	At 104 weeks corrected age
Enrollment:							
Eligibility screen	X						
Informed consent	X						
Demographic data	X						
Allocation		X					
Intervention:							
Hydrocortisone		X					
Placebo		X					
Assessments:							
Baseline variables assessments	X	X					
Primary outcome			X				
Secondary outcomes:							
Brain volume				X			
Others			X				
Long-term outcomes:							
Neurodevelopmental impairment, hearing loss, and blindness							X
Number of readmissions						X	
Weight, length, and head circumference				X	X	X	X
Behavioral problems, premature birth-related mortality							X

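### The stated end of data collection, 31 July 2022, falls 34 to 68 days before the last enrolled infants can reach the 104-week corrected-age visit

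*Protocol article*

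**What the plan says.** The calendar is given once in the protocol article, under Trial status: "Data collection will begin from August 1, 2019, and will end in July 31, 2022".

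Study design sets the accrual time, "The enrollment period will be 1 year", and the length of follow-up, "there will be a series of follow-up for every child until 2 years corrected age". It defines corrected age as the age "which is the revised age from the 40th gestation week for a premature baby". Clinical data collection has one investigator per centre "follow up all patients at 40 weeks PMA and at 12, 26, 52, and 104 weeks corrected age", and Table 1 marks the 104-week visit as close-out.

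The timing of entry comes from two further places. Randomization says "Eligible patients will be randomized at day 28 after birth in each center", and the gestational-age range appears under Participants and again in the Discussion: "restrict the eligible patients to those between 26^+0^ and 30^+6^ weeks gestational age".

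The long-term outcomes tied to the last visit begin with "Neurodevelopmental impairment at 104 weeks corrected age" and include hearing, blindness, behaviour and growth. Mortality is counted from enrolment up to the same age.

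**The concern.** One year of enrolment followed by two years of follow-up looks like three years, and three years is what the calendar provides. But the two years do not start at enrolment. They start at 40 weeks PMA, which every infant reaches some weeks after being randomized at day 28. The calendar leaves no room for those weeks.

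At stake is the final visit of infants enrolled late in the accrual year. If the stated date were applied, they would either have no 104-week assessment or be assessed early, at an age that does not match the outcome definition. Safety is part of the trial's aim, and the Background and Discussion present long-term neurodevelopment as the main worry with postnatal steroids. Clinical data collection says that missing follow-up data will be left out of the analysis, so the article offers no other remedy for these gaps.

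**Working it through.** **Inputs**
- Data collection: 1 August 2019 to 31 July 2022 (Trial status).
- Enrolment: 1 year (Study design). Assumed to open with data collection, so the last day is 31 July 2020. The year then has 366 days.
- Gestational age (GA) at birth: 26+0 to 30+6 weeks, i.e. 182 to 216 days (Participants).
- Randomization: day 28 after birth (Randomization).
- Origin of corrected age: 40 weeks, i.e. 280 days (Study design).
- Last visit: 104 weeks corrected age, i.e. 728 days (Clinical data collection, Table 1).
- Planned total: 196 infants (Sample size calculation). Used only to express the size.

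**Reproducing the stated date.** Two calendar years counted from the last enrolment day: 31 July 2020 + 730 days = 31 July 2022. The stated close is reproduced exactly, but only by counting the two years from enrolment, not from 40 weeks PMA.

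**Time actually needed**

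Days from randomization to last visit = (280 − (GA + 28)) + 728

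Shortfall = days needed − 730

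| GA at birth | PMA at randomization | Days to 40 weeks | Days needed | Visit if enrolled 31 July 2020 | Shortfall |
|---|---|---|---|---|---|
| 26+0 | 30+0 | 280 − 210 = 70 | 70 + 728 = 798 | 7 October 2022 | 68 days |
| 28+6 | 32+6 | 280 − 230 = 50 | 50 + 728 = 778 | 17 September 2022 | 48 days |
| 29+0 | 33+0 | 280 − 231 = 49 | 49 + 728 = 777 | 16 September 2022 | 47 days |
| 30+6 | 34+6 | 280 − 244 = 36 | 36 + 728 = 764 | 3 September 2022 | 34 days |

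The shortfall is thus 48 to 68 days in the lower randomization stratum (26+0 to 28+6) and 34 to 47 days in the upper one (29+0 to 30+6).

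**Age at the stated close.** An infant enrolled on 31 July 2020 would then be 728 − 68 = 660 days (94+2 weeks) corrected if born at 26+0, and 728 − 34 = 694 days (99+1 weeks) if born at 30+6.

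**Share of infants affected, assuming even accrual**
- All infants at 30+6: 34/366 = 9.3%; 0.093 × 196 ≈ 18.
- All infants at 26+0: 68/366 = 18.6%; 0.186 × 196 ≈ 36.

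These are outer bounds. Any real mix of gestational ages lies between them.

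**What is not affected.** The 52-week visit comes at most 70 + 364 = 434 days after randomization, well inside 730. The 12- and 26-week visits and the primary outcome at 36 weeks PMA come earlier still.

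**Start-date assumption.** Baseline data are collected at randomization, so enrolment cannot sensibly precede 1 August 2019. Each day of later opening, or of accrual beyond one year, adds a day to the shortfall.

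**The case against.** The strongest reply is that the design sections commit the trial to seeing every child at 104 weeks, and that the closing date appears only once, as a round three-year calendar. Nothing says that visits stop on that day or that late entrants go unassessed. This stands. A reader might infer that the two-year outcomes of late entrants are lost by design. The documents do not support that: they show two stated terms that conflict, without saying which would yield.

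A reader might also infer that the gap uses up the dropout allowance and leaves the trial short of power. The reserve is 196 − 2 × 81 = 34 infants, and 18 to 36 is about half of it to slightly more than all of it. But that sample size was set for moderate or severe BPD at 36 weeks PMA, which the closing date does not touch. No 104-week outcome has a stated power, so no loss of planned power follows.

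Nor is bias between arms a supported reading. The truncation depends on enrolment date and gestational age, and allocation is blocked and stratified by gestational age within centre, so the arms should be affected about equally. For mortality, only the last weeks before 104 weeks would go unobserved, not the whole outcome.

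A visit window, which an article may leave to the full protocol, could absorb part of the gap. To absorb all of it, the window would have to allow visits 34 to 68 days early, against outcomes fixed at 104 weeks. Nor can data collection be read as hospital data only, since the section headed Clinical data collection includes the visits up to 104 weeks.

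**Conclusion.** The inconsistency is real. One year of enrolment, follow-up of every child to 104 weeks corrected age and a close on 31 July 2022 cannot all hold. The last visits fall 34 to 68 days after the stated close.

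The dates rest on enrolment opening on 1 August 2019, and any later opening makes the gap larger. The figure of 9% to 19% of infants also rests on even accrual, and each end of the range requires every infant to sit at one gestational-age limit.

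If the date were enforced, the cost would be lost precision and under-representation of lower gestational ages in the two-year neurodevelopmental, hearing, vision and behavioural outcomes and in the last growth measurement, with the final weeks of mortality follow-up unobserved. This is a scheduling error limited to the final visit of late entrants. It does not threaten the primary comparison.

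**What to change.** Define the end of data collection as the 104-week corrected-age visit of the last enrolled infant. For enrolment to 31 July 2020 that is no earlier than 7 October 2022, plus any visit window. Defined by the event, the end moves with accrual if enrolment opens late or overruns. Correct the date under Trial status to match.

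The cost is a date amendment and about 10 more weeks of follow-up (68 days), consisting of visits already planned, with no new procedures or patients.

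Closing enrolment early is not a good alternative. Keeping 31 July 2022 for infants born at 26+0 would mean stopping on 24 May 2020. At even accrual that gives up 68/366 of the year, about 36 infants, for a primary outcome that the closing date does not affect.

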## Data Availability

The authors declare that all relevant data will be included in the article or supplementary files. Additional data are available from the corresponding author on reasonable request.

## Abbreviations

BPD: Bronchopulmonary dysplasia
PND: Postnatal day
NICHD: National Institute of Child Health and Human Development
PMA: Postmenstrual age
GA: Gestational age
HC: Hydrocortisone
RCT: Randomized controlled trial
GCP: Good Clinical Practice
GMP: Good Manufacturing Practice
IVH: Intraventricular hemorrhage
PVL: Periventricular leucomalacia
NEC: Neonatal necrotizing enterocolitis
ROP: Retinopathy of prematurity
CPAP: Continuous positive airway pressure
ITT: Intention to treat
CONSORT: Consolidated Standards of Reporting Trials
CRFs: Case report forms
